## Methods and analysis

### Study design

This is a prospective national observational cohort study which includes all kidney patients who were vaccinated against SARS-CoV-2 in the Dutch vaccination programme. Currently available vaccines in the Netherlands are the mRNA-1273 (Moderna), BNT162b2-mRNA (Pfizer), ChAdOx1 nCoV-19 (AstraZeneca) and Ad26.COV2.S (Janssen) vaccines [5–8]. Patients with CKD stages G4-G5 or on KRT received prioritization as medical high-risk group and predominantly received the mRNA-1273 vaccine in the Dutch vaccination programme. To assess the antibody dependent immune response after vaccination, blood samples will be collected at 28 days and at 6 months after the second vaccination with a home-based finger prick test. Antibody measurement will include both the receptor binding domain (RBD) of the spike (S) antigen and the nucleocapsid (N) antigen [15]. Combining these antibody measurements allows to distinguish a natural infection from an antibody response after S1-based vaccination.

Questionnaires will be obtained during a two-year follow-up period to assess the incidence of COVID-19 or (serious) adverse events ((S)AEs) after vaccination. The study events are demonstrated in Fig. 1. The questionnaires are shown in the supplemental materials.

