### Statistical considerations

Baseline characteristics of vaccinated patients with CKD stages G4-G5 or on KRT will be compared with non-vaccinated patients with CKD stages G4-G5 or on KRT and the vaccinated general population using a two-sample t-test in case of continuous variables (or a Mann-Whitney U-test if data are not normally distributed), and a Pearson Chi-2 test in case of categorical variables.

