#### Analysis of primary endpoint

Incidence rates of COVID-19 within 2 years after vaccination will be reported for each study population separately and incidence rates will be compared. Primary comparisons are comparisons of COVID-19 incidence rates in vaccinated patients versus non-vaccinated patients and versus the vaccinated general population. These comparisons will be made separately for patients with CKD stages G4-G5 or on KRT. For comparison of incidence rates, we will calculate crude hazard ratios. Vaccine efficacy will be reported as 100 × (1- hazard ratio). We will calculate model adjusted hazard ratios using multivariable Cox-regression, in case of imbalance in study populations regarding relevant characteristics, such as age, sex, comorbidity, kidney replacement modality and use of immunosuppressive agents. Cause specific hazard ratios will be estimated to account for competing risk of mortality. Starting date of follow-up will be the date of second vaccination in vaccinated patients. Starting date of follow-up in non-vaccinated patients will be the same date (or +/− 7 days from date of vaccination) as date of vaccination in the matched vaccinated patients to account for changes in incidence of COVID-19 over time. Non-vaccinated patients will be censored at the day of vaccination in case they are vaccinated before the end of follow-up. The aforementioned analyses will be repeated in patients with and patients without evidence of prior infection. Among vaccinated patients, incidence rates will also be compared across the various vaccines that will be used. For this purpose, vaccinated patients with CKD stages G4-G5 or on KRT and general population again will be analysed separately.

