#### Analysis of secondary endpoints

##### Efficacy - Antibody response

Participants will be classified as responders or non-responders [17]. Number and proportion of responders and non-responders at day 28 will be reported for each patient population. Pearson chi-2 test will be performed to assess whether antibody response differ between patient groups. In subsequent sensitivity analyses we will perform multiple regression analyses correcting for possible differences in age and sex between the patient groups. Additionally, in kidney transplant recipients we will investigate whether time after transplantation, and the different immunosuppressive regimens are associated with response rate.

To assess durability of response within each patient group, we will report and compare response at day 28 with response at month 6 after vaccination. Comparison will be made using McNemar test.

The association between antibody response after SARS-CoV-2 vaccination and protection against COVID-19 will be examined for each patient group separately. For this, we will compare the antibody response at 28 days after vaccination in patients who develop COVID-19 with the antibody response in patients who did not develop COVID-19. Similar comparison will be made at 6 months after vaccination. We will examine this by use of the t-test or if more appropriate a non-parametric test. Subsequently, in a logistic regression model using Youden’s index, a cut-off in the antibody response at 28 days will be defined to serve as a correlate of protection against COVID-19.

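### The crude hazard ratio is the default in a non-randomised comparison, adjustment depends on an undefined imbalance check, and the hazard ratio behind vaccine efficacy is not named

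*Protocol article*

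**What the plan says.** All references are to the protocol article.

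- **Study design** describes an observational cohort: "This is a prospective national observational cohort study which includes all kidney patients who were vaccinated against SARS-CoV-2 in the Dutch vaccination programme". Vaccination is not randomised.
- **Analysis of primary endpoint** names two primary comparisons: "Primary comparisons are comparisons of COVID-19 incidence rates in vaccinated patients versus non-vaccinated patients and versus the vaccinated general population".
- The estimate given without any condition is the unadjusted one: "For comparison of incidence rates, we will calculate crude hazard ratios".
- The efficacy measure follows directly: "Vaccine efficacy will be reported as 100 × (1- hazard ratio"). Crude or adjusted is not specified.
- Adjustment comes next and is conditional: "We will calculate model adjusted hazard ratios using multivariable Cox-regression, in case of imbalance in study populations regarding relevant characteristics". The characteristics are an open list: "such as age, sex, comorbidity, kidney replacement modality and use of immunosuppressive agents".
- **Statistical considerations** holds the only baseline comparison described. It consists of significance tests, "using a two-sample t-test in case of continuous variables" with a rank test as alternative, and a chi-square test for categorical variables. No threshold for imbalance appears there or in the primary analysis.
- The same primary-analysis section aligns the start of follow-up of non-vaccinated patients with that of matched vaccinated patients (within 7 days), to allow for changing COVID-19 incidence. It uses cause-specific hazards for competing death and repeats the analyses by evidence of prior infection.
- **Safety** analyses mortality and the other safety outcomes in a similar way, so the same rule carries over.

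**The concern.** In a cohort, the reason to adjust for a characteristic is prior knowledge that it predicts both vaccination and COVID-19. Whether it looks unbalanced in the sample at hand is a different question. The plan makes the existence of an adjusted estimate depend on that second question, without saying how it is answered or by whom.

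Two consequences follow. If no imbalance is declared, the only estimate is the crude HR, with whatever confounding it carries. If imbalance is declared, an adjusted HR is produced, but the text leaves open whether it replaces the crude one as the source of VE and whether the model holds all the named characteristics or only the unbalanced ones. The primary number can thus be chosen after the data are seen.

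If imbalance is judged by significance tests, the trigger also depends on group size, while the bias in the HR does not. The number of non-vaccinated patients is not stated.

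**Working it through.** **No figure to reproduce.** The article gives no alpha, target HR, event rate, covariate distribution or number of non-vaccinated patients. The arithmetic below is an illustration with assumed inputs. The finding itself rests on the wording.

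**Step 1: does another part of the plan make adjustment unconditional?**

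| Element | What it addresses | Does it remove the condition? |
|---|---|---|
| Start-date alignment | Calendar time (its only stated purpose) | No |
| Cause-specific hazards | Competing death | No |
| Repeat by prior infection | Prior infection, within strata | No; the same crude-first rule applies in each stratum |
| Separate analysis by patient population | Differences between kidney populations | No |

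**Step 2: size of the bias from one factor.** Assumed: a binary factor with HR 2 for COVID-19, prevalence 25% in one group and 30% in the other, true VE 60% (HR 0.40). Approximation for uncommon events:

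bias factor = (1 + p_vaccinated × (2 − 1)) / (1 + p_non-vaccinated × (2 − 1))

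- Commoner in the non-vaccinated: 1.25 / 1.30 = 0.9615. Crude VE = 1 − 0.40 × 0.9615 = 61.5%.
- Commoner in the vaccinated: the inverse. Crude VE = 1 − 0.40 / 0.9615 = 58.4%.

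The shift is about 1.5 percentage points either way.

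**Step 3: would a test flag it?** Assumed: 4,000 vaccinated with 25%, a smaller non-vaccinated group with 30%, two-sided 5% two-proportion test. For 300 non-vaccinated:

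- pooled proportion = (1,000 + 90) / 4,300 = 0.2535; null standard error = 0.0260
- standard error under the alternative = √(0.25 × 0.75 / 4,000 + 0.30 × 0.70 / 300) = 0.0273
- power = Φ((0.05 − 1.96 × 0.0260) / 0.0273), which is 0.48 with unrounded standard errors

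| Non-vaccinated | Chance that 25% v 30% is flagged |
|---|---|
| 200 | 36% |
| 300 | 48% |
| 4,000 | 99.9% |

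The bias in step 2 is the same in every row; only the trigger changes.

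**Step 4: a larger imbalance.** For 25% v 35% and HR 2, the factor is 1.25 / 1.35 = 0.926, so a VE of 60% reads as 63.0% or 56.8%. With 300 non-vaccinated, the test flags this about 96% of the time (87% with 200). A bias of this size from a single factor would therefore usually trigger the rule.

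**Step 5: several modest imbalances.** Three independent factors like the one in step 2, all in the same direction: 0.9615³ = 0.889. VE of 60% then reads as 1 − 0.40 × 0.889 = 64.4%, or 1 − 0.40 / 0.889 = 55.0%. At 48% each, the chance that at least one is flagged is 1 − 0.52³ = 86%. The plan does not say whether one flag brings all three into the model.

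**The case against.** The strongest reply is that adjustment is already written into the primary analysis and will almost certainly happen. Across five named characteristics in an observational comparison, some imbalance is very likely. At 48% per factor, five independent factors give 1 − 0.52⁵ = 96% for at least one flag. Large single imbalances would nearly always be caught, and those likely to be missed bias VE by only a point or two. This stands, and it limits the size of the problem. It does not settle which HR defines VE or what enters the model. If adjustment is nearly certain anyway, the condition serves no purpose.

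A second reply is that the text never equates imbalance with p < 0.05, nor refers back to the baseline tests. That is correct: the link is the natural reading, but an inference. Without it, the trigger is simply undefined.

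A third is that the reference to matched vaccinated patients may imply matching on more than date. A condensed article may omit criteria, but the only purpose it states is calendar time.

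A reader might also infer that prior infection is ignored because it is missing from the covariate list. The article does not support this: the list is open, and the analyses are repeated by prior-infection status. Nor does the antibody analysis share the defect. There the regression is planned without a trigger: "In subsequent sensitivity analyses we will perform multiple regression analyses correcting for possible differences in age and sex between the patient groups". Placing it as a sensitivity analysis of a secondary endpoint is a separate choice.

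**Conclusion.** The point holds in its wording. The primary analysis makes the crude HR the default for both comparisons, adds adjustment on an undefined condition, and leaves open which HR becomes VE. The primary result can be confounded, and whether it is adjusted depends on the data.

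Its size cannot be determined from the article. Under the assumed inputs, one 5-point imbalance in a factor with HR 2 moves a VE of 60% to about 58.4% or 61.5%, and is flagged about half the time with 4,000 v 300 patients. Several such factors in the same direction accumulate.

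A reader might infer that shifts of several points from a single factor would pass unnoticed. The arithmetic does not support that: the 10-point imbalance that produces them would be flagged about 96% of the time at these numbers. Nor does the article say that the reported VE will be crude; it leaves this open.

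**What to change.** In **Analysis of primary endpoint**:

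1. Delete the clause that makes adjustment conditional on imbalance.
2. State that reported VE is always 100 × (1 − adjusted cause-specific HR), and that the crude HR is shown for reference only.
3. Fix the covariates in advance for each comparison:
   - Vaccinated v non-vaccinated patients: at least age, sex, comorbidity, kidney replacement modality (where it applies), immunosuppressive agents and COVID-19 before the start of follow-up.
   - Patients v vaccinated general population: the variables that the national public health institute (RIVM) data provide, without modality, which does not apply to those controls.
4. In **Statistical considerations**, describe balance with standardised differences and let no test result decide the model.

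**Cost.** For patient-versus-patient comparisons this is essentially wording: the Cox model is already named and the listed items are all in Table 2. The general-population comparison needs a check of what RIVM can supply, so the cost there is not established by the article. The functional form of age and the exact comorbidity terms can be left to the analysis plan, provided they are fixed before outcome data are seen.

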### Setting

The study starts in April 2021 amidst the COVID-19 pandemic when the Dutch vaccination program has started to vaccinate high-risk patients, including patients with kidney disease. COVID-19 incidence rates are still high and the health care system has not yet regained full capacity to exert routine care to all patients, due to lack of capacity.

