### Outcome definitions

For an overview of the clinical endpoints in this study we refer to Table 3.

**Table 3 Tab3:** Clinical endpoints LESS-CoV-2 study

*Primary endpoint*	
Incidence (per person-year) of COVID-19 in a two-years period after SARS-CoV-2 vaccination in patients with CKD stage G4-G5 or on KRT.	
*Secondary endpoints*	
Efficacy	
• The antibody based immune response to SARS-CoV-2 vaccination at 28 days after SARS-CoV-2 vaccination.	
• The durability of the antibody response at 6 months after SARS-CoV-2 vaccination	
Safety	
• Incidence of mortality	
• Incidence of AEs of specific interest as defined by (inter) national authorities	
• Incidence of a combined endpoint of acute rejection or graft failure in kidney transplant recipients	
• Incidence of HLA antibodies defined as cPRA > 5% in dialysis patients on the waiting list for their first kidney transplantation	
*Exploratory endpoints*	
Vaccination coverage rates	
Disease severity in patients who develop COVID-19, assessed as	
• Hospitalization	
• ICU admission	
• Mechanical ventilation	
PROMs in patients on dialysis	
SARS-CoV2 genotype in patients with COVID-19 (in case available)	

*COVID-19* Coronavirus Disease 2019, *SARS-CoV-2* Severe Acute Respiratory Syndrome Coronavirus-2, *CKD* Chronic Kidney Disease, *KRT* Kidney Replacement Therapy, *AEs* Adverse Events, *HLA* Human Leukocyte Antigen, *cPRA* Calculated Panel Reactive Antibody, *ICU* Intensive Care Unit, *PROMs* Patient Reported Outcome Measures

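### Efficacy is counted from the day of the second dose, so COVID-19 acquired before that dose or its response counts as vaccine failure; a lagged analysis should be reported with the day-0 result.

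*Protocol article*

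**What the plan says.** The protocol article (Analysis of primary endpoint) fixes time zero for vaccinated patients: "Starting date of follow-up will be the date of second vaccination in vaccinated patients". Matched non-vaccinated patients start on the same calendar date, within 7 days either way, and are censored if they are later vaccinated. Efficacy is 100 times one minus the hazard ratio.

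The endpoint in Table 3 (Outcome definitions) is consistent with that start: "Incidence (per person-year) of COVID-19 in a two-years period after SARS-CoV-2 vaccination". There are two main contrasts: "Primary comparisons are comparisons of COVID-19 incidence rates in vaccinated patients versus non-vaccinated patients and versus the vaccinated general population".

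The article states no lag, excludes no early cases and plans no analysis with a later start. The analyses are to be repeated by evidence of prior infection, and cause-specific hazards are planned because of competing mortality.

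**The concern.** COVID-19 that appears in the days just after the second dose may have been acquired before that dose or before the response to it. Under the stated rule such a case counts as failure of the completed schedule. The reported efficacy is then a blend of an early period and the later period of established protection.

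None of the stated safeguards separates the two. Calendar matching handles changes in background incidence, not delayed protection. The prior-infection split is not said to remove infections incubating at the second dose. Cause-specific hazards deal with death.

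The study hypothesis is that kidney patients gain less protection. In the contrast with non-vaccinated patients, a dilution of this kind would move the estimate in the direction of that hypothesis. If the response develops more slowly in some patient groups, the dilution could also differ between groups that are reported separately.

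**Working it through.** The article gives no efficacy, event or power figure that bears on this point, so there is no stated figure to reproduce. The check is of direction and possible size.

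**Inputs from the article:** start at the second dose; matched controls start on the same date within 7 days; controls are censored at their own vaccination; follow-up is 2 years (about 730 days).

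**Assumed inputs (not in the article):** established efficacy 70% (hazard ratio 0.30); net efficacy 30% in the first 14 days (hazard ratio 0.70); constant background incidence; the control times shown below.

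**Formula.** Vaccinated time informs the Cox comparison only while controls are still at risk. The estimate is therefore approximated by weighting on the share *f* of control time that falls in the early window:

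HR = 0.30 + (0.70 − 0.30) × *f*

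| Control time | *f* | HR | Efficacy | Loss (points) |
|---|---|---|---|---|
| Spread over 730 days | 14/730 = 0.019 | 0.308 | 69.2% | 0.8 |
| Average 90 days | 14/90 = 0.156 | 0.362 | 63.8% | 6.2 |
| Average 60 days | 14/60 = 0.233 | 0.393 | 60.7% | 9.3 |

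**Refinement.** Using 14 divided by the average assumes that every control stays at least 14 days. If control times are exponential with the same averages, *f* = 1 − exp(−14/mean):

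- Mean 90 days: *f* = 0.144, HR = 0.30 + 0.40 × 0.144 = 0.358, efficacy 64.2%, loss 5.8 points.
- Mean 60 days: *f* = 0.208, HR = 0.30 + 0.40 × 0.208 = 0.383, efficacy 61.7%, loss 8.3 points.

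**Wider range.** Keep established efficacy at 70%, let the window be 7 to 14 days and early efficacy 0% or 35%. Let controls leave at a constant rate *r* = ln 2/median, so that for a window of L days *f* = (1 − exp(−*r*L))/(1 − exp(−730*r*)).

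| Controls | Early share | Estimated efficacy |
|---|---|---|
| Unvaccinated throughout 2 years | 1.0 to 1.9% | 68.7 to 69.7% |
| Median 60 days to vaccination | 7.8 to 14.9% | 59.5 to 67.3% |
| Median 30 days | 14.9 to 27.6% | 50.7 to 64.8% |
| Median 14 days | 29 to 50% | 35.0 to 59.7% |

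**Direction.** The loss equals *f* × (later efficacy − early efficacy). It is zero if the two are equal and changes sign if net early efficacy is the higher.

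**Second contrast.** Against the vaccinated general population both groups have an early window after the dose. Where protection is weak in both, the early ratio reflects mainly their underlying risks. The overall ratio then moves towards 1 if those risks are similar, and is otherwise distorted. This contrast is not an efficacy against no vaccination.

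**The case against.** **This is a choice of estimand.** The endpoint is incidence after vaccination, and the start date agrees with it. Starting matched pairs on the dose date requires no event-free survival after the dose, which is a real merit. This stands as a reason to keep the day-0 analysis in the report. It does not help a reader who takes the figure as the protection given by the completed schedule.

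**The bias need not run downwards.** Patients enter at their second dose and may already have first-dose protection, which would soften the effect. Ill patients may defer the dose, which would raise apparent early efficacy and could offset it. This stands, and the direction is therefore conditional.

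**The early weeks may carry little weight.** A reader might infer that they drive the hazard ratio, because controls leave at vaccination, these patients were prioritised (Study design), and at the start "COVID-19 incidence rates are still high". The article does not support that. It gives no vaccination times for controls, and those still unvaccinated when their match receives a second dose may stay so for long. The remark on incidence gives no rate and describes only the start of the study. Even at averages of 60 or 90 days, about 77% or 84% of the weight lies after day 14.

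**Day 28 does not mark the onset of protection.** A reader might take "The antibody based immune response to SARS-CoV-2 vaccination at 28 days after SARS-CoV-2 vaccination" as the plan's own view of when protection begins. It is only the antibody sampling time for a secondary endpoint.

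**Detail may sit in a fuller document.** A sensitivity analysis with another start date could well be specified there, and its absence here is no fault. The start date itself, however, is stated outright in the article.

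**Conclusion.** The point holds as a minor one. The article fixes the day of the second dose as time zero for the efficacy measure, and none of its other rules removes infections that precede the response to that dose. If net early protection is below later protection, the ratio against non-vaccinated patients is pulled towards 1.

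Under the assumed 70% and 30%, the loss runs from under 1 point to about 6 or 9 points, depending on how long controls remain unvaccinated. The article cannot settle which applies. One might conclude that the design necessarily understates efficacy, or does so in both main contrasts. The documents support neither: the first depends on net early protection, and the contrast with the general population does not measure efficacy in that sense.

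**What to change.** For the COVID-19 efficacy endpoint only:

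- Prespecify a lag after the second dose before cases are counted (for example 14 days), with its length justified by the investigators.
- Start each matched non-vaccinated patient at the same lagged calendar date, and require both members of the match to be uncensored and free of COVID-19 since the dose date.
- Apply the same lag to the vaccinated general population.
- Report the day-0 analysis beside the lagged one.
- Do not lag the safety endpoints.

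The cost is a sentence or two in the plan and a shifted start date; no new data on kidney patients are needed. For the general population, the national institute's data must allow counting from the lagged date. The statistical price is that early events leave the lagged estimate, which also conditions on remaining event-free and uncensored through the lag. For that reason the two results should be shown together.

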**Methods:**

In this national prospective observational cohort study we will follow patients with CKD stages G4-G5 or on KRT (*n* = 12,000) after SARS-CoV-2 vaccination according to the Dutch vaccination program. Blood will be drawn for antibody response measurements at day 28 and month 6 after completion of vaccination. Patient characteristics and outcomes will be extracted from registration data and questionnaires during 2 years of follow-up. Results will be compared with a control group of non-vaccinated patients. The level of antibody response to vaccination will be assessed in subgroups to predict protection against COVID-19 breakthrough infection.

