##### Safety

Incidence rates of (S)AEs, mortality, acute rejection, graft failure or HLA antibodies will be calculated and compared across patient groups in analyses similar to analysis of the primary outcome.

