## Discussion

In the LESS-CoV-2 study we will assess the efficacy and safety of the mRNA-1273, BNT162b2, ChAdOx1 nCoV-19 and Ad26.COV2.S SARS-CoV-2 vaccines in Dutch patients with CKD stages G4-G5, on dialysis or after kidney transplantation.

We expect to determine an antibody response cut-off value which allows to predict protection against COVID-19 breakthrough infection after completion of SARS-CoV-2 vaccination. This contributes to the establishment of surrogate endpoints which will facilitate the development and approval of new vaccines [18]. In this study, we will identify non-responders by means of an insufficient antibody response after SARS-CoV-2 vaccination. This population can be offered a booster vaccine or an alternative vaccine to assess whether or not a sufficient antibody response can still be achieved.

Furthermore, we will address the safety of SARS-CoV-2-vaccination in patients with severe kidney insufficiency and in those that are treated with immunosuppressive drugs. Since these patients were not sufficiently represented in the large registration studies of the various vaccines, specific AEs associated with kidney failure and its treatment may not have been recognized so far. In addition, rare but possibly harmful AEs must be searched for in pharmacovigilance studies after widespread distribution of the vaccines. Recent reporting of vaccine-induced immune thrombotic thrombocytopenia caused by the ChAdOx1 nCoV-19 and Ad26.COV2.S SARS-CoV-2 vaccines is a possible example of such a rare complication [19]. It is essential to collaborate with large registry studies to be able to detect rare SAEs in patients with kidney disease. Different SARS-CoV-2 vaccines are administered to our subjects, and for that reason we will monitor the development of immunisation against HLA-antigens, allograft rejection and/or kidney transplant failure following SARS-CoV-2 vaccination.

Considering that items such as mental QoL, anxiety and depression may be positively influenced by vaccination, it is highly relevant to monitor the effect of SARS-CoV-2 vaccination on patient reported outcome measurements (PROMs). In our cohort of dialysis patients PROMs have been monitored since 2019. During the study we will further monitor the course of mental health of vaccinated and non-vaccinated dialysis patients and compare this to pre-COVID-19 pandemic era and the COVID-19 pandemic era without vaccines.

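### The only stated start of follow-up is the second dose, so as written the safety analysis omits events between doses, and one-dose recipients have no start date

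*Protocol article*

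**What the plan says.** Under Analysis of primary endpoint, the protocol article sets the clock for the vaccinated group: "Starting date of follow-up will be the date of second vaccination in vaccinated patients". For controls it says: "Starting date of follow-up in non-vaccinated patients will be the same date (or +/− 7 days from date of vaccination) as date of vaccination". The date meant is that of the person with whom the control is paired. On censoring it says: "Non-vaccinated patients will be censored at the day of vaccination in case they are vaccinated before the end of follow-up". Neither control rule names the dose.

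Under Safety, the rates of (serious) adverse events, mortality, acute rejection, graft failure and HLA antibodies are to be "calculated and compared across patient groups in analyses similar to analysis of the primary outcome". No separate start date is given.

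The Fig. 1 legend puts the first vaccination at t = -1 and the second at t = 0. For blood sampling, the abstract uses a different anchor: "Blood will be drawn for antibody response measurements at day 28 and month 6 after completion of vaccination". Study enrolment also speaks of completion, whereas Study design counts from the second vaccination. Four products are in scope, Ad26.COV2.S among them, and incidence is to be compared across the vaccines used.

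**The concern.** A start at the second dose can be defended for efficacy in people who complete a two-dose course. It suits safety poorly, because exposure begins with the first dose. If the safety analysis inherits the efficacy clock, the vaccinated cohort consists of people who survived dose 1 and went on to dose 2. Harm that occurs between the doses, or that prevents the second dose, is then not charged to vaccination. Covariate adjustment cannot repair this, because the patients concerned are not in the vaccinated group at all.

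Safety is a stated objective, and the Discussion stresses rare events: "It is essential to collaborate with large registry studies to be able to detect rare SAEs in patients with kidney disease". It gives as its example a rare thrombotic complication linked to two of the products in scope, one of them Ad26.COV2.S.

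Separately, a vaccinated patient with a single dose has no time zero, so cannot be placed in the primary analysis or in the comparison between vaccines.

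**Working it through.** The plan has no figure of its own on this point to reproduce. The check is a reading of the text, followed by an illustration under stated assumptions.

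**1. Which clock applies to safety?** The start-date sentence stands under the primary endpoint. The Safety paragraph points back to that analysis and offers nothing else, so dose 2 is the only start date a reader can apply.

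**2. Do the control rules bring the between-dose time back in?** The dose that triggers censoring is not named, so there are two readings:

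| Censoring dose | Time between doses is counted as | Effect on harm after dose 1 |
|---|---|---|
| Dose 1 | neither group | absent from the comparison |
| Dose 2 | non-vaccinated | charged to the controls |

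Neither reading counts such harm against vaccination. The second makes vaccination look safer still.

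**3. Who has no start date?** Anyone without a second dose: patients who die or stop after dose 1, and recipients of any product given as a single dose. The article does not state the number of doses per product. If Ad26.COV2.S is given once (an assumption), its recipients have no time zero, although the article plans to assess that vaccine and to compare vaccines.

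**4. Second dose or completion?** The two anchors coincide for a two-dose course and differ for a one-dose course. Study design and Analysis of primary endpoint use the former; the abstract and Study enrolment use the latter, for blood sampling only.

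**5. Share of time omitted.** Let d be the interval between doses in days (assumed; not in the article). Follow-up after dose 2 is two years, 2 × 365.25 = 730.5 days.

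Share omitted = d / (730.5 + d)

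- d = 21: 21 / 751.5 = 2.8%
- d = 28: 28 / 758.5 = 3.7%
- d = 42: 42 / 772.5 = 5.4%
- d = 84: 84 / 814.5 = 10.3%

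**6. Deaths that would fall in the gap.** The abstract gives n = 12,000. Assume that all receive a first dose and that annual mortality r is 2% to 15% (not in the article).

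Expected deaths = 12,000 × r × d / 365.25

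- d = 21: 12,000 × 0.02 × 21 / 365.25 = 14; with r = 0.15, 103
- d = 84: 12,000 × 0.02 × 84 / 365.25 = 55; with r = 0.15, 414

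These are deaths from any cause, not vaccine-related deaths. They show how many events the rule would exclude, not the size of a bias.

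**7. Two related choices, on common horizons.** All risks here are assumed.

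- *No post-dose risk window.* A rate ratio of 3 for 42 days after dose 2 averages to 1 + 2 × 42/730 = 1.12 over 730 days, and to 1 + 2 × 42/182 = 1.46 over 182 days.
- *COVID-19 counted from day 0.* Take a hazard ratio of 0.5 in the first 14 days and 0.1 afterwards. Over 730 days the average is (14 × 0.5 + 716 × 0.1)/730 = 0.108, an efficacy of 89.2% against 90%. Over 182 days it is (14 × 0.5 + 168 × 0.1)/182 = 0.131, an efficacy of 86.9%.

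Dilution of the safety signal is largest on the long horizon, and the efficacy lag is largest on the short one. They cannot both be large at once.

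**The case against.** The strongest objection is that the start-date sentence belongs to the primary endpoint, and that the Safety paragraph calls for similar, not identical, analyses. A condensed article may leave the safety clock to the full protocol or analysis plan. This stands in part: the extension to safety is an inference, which limits confidence. But the article does state a rule, gives no other, and refers safety back to it. That goes beyond a detail left out.

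A reader might infer that every adverse event and death after the first dose is lost. The article does not support that. Events after dose 2 are counted in those who receive it. Nor is collection restricted: the questionnaires cover events after vaccination without naming a dose, all registry-eligible patients are followed for adverse events and vaccination status, and dose 1 is on the timeline. The gap lies in the analysis, not in the data.

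A reader might also infer a plan to compare rejection in patients who have no graft. Table 3 rules that out by defining the endpoint as "Incidence of a combined endpoint of acute rejection or graft failure in kidney transplant recipients"; HLA antibodies are likewise confined to wait-listed dialysis patients. The phrase about patient groups is loose wording, and a comparison of vaccinated with non-vaccinated patients inside the relevant group remains available.

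Two further points stand. Counting COVID-19 from day 0 and omitting a fixed risk window are legitimate choices that contradict nothing in the article. And since patients predominantly received mRNA-1273, the one-dose group may be small.

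**Conclusion.** The point holds in a limited form. As written, the safety analysis starts at dose 2, between-dose events fall outside it, patients who do not go on to dose 2 never enter the vaccinated group, and one-dose recipients have no start date for either analysis.

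If there is excess harm between the doses, the bias is towards a finding of safety. An excess confined to that interval would leave the reported hazard ratio at 1, whatever its size; without such an excess, the omission costs information but need not distort the ratio. The omitted time is 2.8% to 10.3% of the total for assumed intervals of 21 to 84 days.

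This should be fixed before analysis. Confidence is medium, because the conclusion requires that a similar analysis include the same time zero.

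**What to change.** - **Safety:** start follow-up at the first dose, include everyone with at least one dose, and match non-vaccinated controls on that date.
- **Efficacy:** set time zero at completion of the schedule for the product received. Reconcile Study design and Analysis of primary endpoint with the abstract and Study enrolment, so that one anchor is used throughout.
- **Controls:** name the dose that sets the matching date and the censoring date. Censor at the first dose, so that time after dose 1 is never counted as non-vaccinated.
- **Optional sensitivity analyses:** COVID-19 counted from day 14 in both groups, and a post-dose risk window for safety.

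The cost is mainly a few sentences of analysis wording. Dose 1 is already on the study timeline and vaccination status is already collected. The safety analysis will need its own set of matched control dates, separate from those for efficacy.
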